**IRB Approved**

**06/24/13**

[figure not shown]

interactions with other commonly used antiretroviral agents, especially the currently available protease inhibitors and non-nucleoside reverse transcriptase inhibitors. Specifically, there is no potential or need for boosting with CYP3A4 inhibitors such as ritonavir. Also, unlike most protease inhibitors, and even NNRTIs, Raltegravir does not seem to increase lipid levels.

In protocol 004, Raltegravir (administered in doses ranging from 100 mg bid to 600 mg bid), in combination with Tenofovir and Emtricitabine for 24 weeks was not associated with any elevation in total cholesterol, LDL-cholesterol or triglyceride levels, in contrast to Efavirenz in combination with Tenofovir and Emtricitabine.[10, 11] (Teppler et al., 46th ICAAC, poster 0256a). The combination of Raltegravir with a potent PI with a mild metabolic profile will likely yield an even better response among naïve patients, while preventing treatment-limiting toxicities. This is likely to be the first real chance at a potent NRTI-free regimen for use in naïve patients.

Darunavir is currently approved for use in HAART-experienced patients at the dose of 600 mg bid with ritonavir boosting.

Darunavir is the newest PI approved for patients who are highly treatment-experienced or have HIV-1 strains resistant to multiple PIs based on demonstrated activity against PI-resistant viruses.

The safety and efficacy of Darunavir has been extensively explored, primarily in the POWER 1, 2 and 3 trials (Darunavir/ritonavir compared to other PIs in treatment-experienced patients), the TITAN trial (Darunavir/ritonavir compared to Lopinavir/ritonavir in treatment-experienced patients) and the ARTEMIS trial (Darunavir/ritonavir compared to lopinavir/ritonavir in treatment-naïve patients).

POWER 1 and 2 are two randomised, multinational, phase IIB studies conducted to evaluate the efficacy and safety of darunavir in combination with low-dose ritonavir in treatment-experienced HIV-1-infected patients. A pooled subgroup analysis of their results at week 48 for patients receiving the recommended dose of darunavir-ritonavir compared with those receiving other protease inhibitors (PIs) was recently published [13].

At week 48, 67 of 110 (61%) darunavir-ritonavir patients compared with 18 of 120 (15%) of control PI patients had viral load reductions of 1 log10 copies per mL or greater from baseline (primary endpoint; difference in response rates 46%, 95% CI 35%-57%,  $p < 0.0001$ ). Based on a logistic regression model including stratification factors (baseline number of primary PI mutations, use of enfuvirtide, baseline viral load) and study as covariates, the difference in response was 50% (odds ratio 11.72, 95% CI 5.75-23.89). In the darunavir-ritonavir group, rates of adverse events were mostly lower than or similar to those in the control group when corrected for treatment exposure. No unexpected safety concerns were identified.

In the TITAN trial, 595 treatment-experience LPV/r and DRV/r-naïve patients were randomized to receive DRV/r (600 mg/100 mg bid) vs LPV/r (400 mg/100 mg bid) + optimized background. After 48 weeks a significantly higher proportion of people assigned to darunavir had a viral load below 400 (77% vs. 67%) or 50 copies (71% vs. 60%). Darunavir was found to be non-inferior and superior to lopinavir ( $P = 0.008$ ).

The ARTEMIS study compared darunavir/ritonavir (800/100mg once daily) with lopinavir/ritonavir (once or twice daily), both in combination with tenofovir/emtricitabine,

**IRB Approved**

**06/24/13**

[figure not shown]

in a randomized, open-label, non-inferiority trial [14]. The study enrolled 689 treatment-naïve subjects with a median CD4 count of 228 cells/mm^3, and a median plasma HIV RNA level of 60,000-70,000 copies/mL. At 48 weeks, plasma HIV RNA was <50 copies/mL in 84% of darunavir/ritonavir recipients and 78% of lopinavir/ritonavir recipients ( $p < 0.001$ ). In subgroup analysis, DRV/r QD was superior to LPV/r (overall) in patients with baseline viral load  $\geq 100,000$  copies/mL. The DRV/r QD group experienced a lower incidence of lipid abnormalities than the lopinavir/ritonavir group. Grade 2 to 4 adverse events, primarily diarrhea, were seen in 7% of darunavir/ritonavir recipients and 14% of lopinavir/ritonavir recipients ( $p = 0.01$ ). Moreover, trough concentrations of once-daily darunavir/ritonavir stayed above the 50% effective concentration (EC50) for wild-type (nonmutant) virus in everyone taking these protease inhibitors (PIs) in the ARTEMIS trial of first-line regimens [15]

We therefore plan to analyze the safety and efficacy of Raltegravir and once-daily boosted Darunavir in HAART-naïve patients, compared to an approved DHHS first-line regimen.

### 3.2 STUDY PROCEDURES

#### 3.2.1 Concomitant Medication(s)/Treatment(s)

The study patients cannot be concomitantly on any other antiretroviral drugs than the ones outlined in the respective treatment arms. The concomitant use of other medications/therapies is allowed unless specifically prohibited in the Prohibited Concomitant Medications/Therapies section below.

#### Prohibited Concomitant Medications/Therapies

Raltegravir is eliminated mainly via the UDP-glucuronosyltransferase (UGT)1A1-mediated glucuronidation pathway and, therefore, the compound may be subject to drug-drug interactions when co-administered with drugs that are known to be UGT1A1 inducers or inhibitors. However, Raltegravir is not anticipated to affect the metabolic clearance of drugs metabolized by UGT1A1 given its low UGT1A1 inhibitory (IC50 for the inhibition of UGT1A1  $> 50 \mu\text{M}$ ) and induction potential. Since Raltegravir is neither an inducer nor inhibitor of cytochrome P-450 enzymes, it is not expected to result in metabolic drug interactions with substrates of cytochromes P-450.

1. The medications/therapies below are contraindicated in this study because they are potent broad inducers of drug metabolism, inducers of CYP3A (thus potential inducers of glucuronidation), and their coadministration with Raltegravir will likely result in altered (lowered) drug levels of Raltegravir:
  - a. Phenobarbital
  - b. Phenytoin
  - c. Rifampin
2. Medications/therapies that may adversely affect the drug levels of the other ARTs used in the three study arms should be avoided to ensure adequate therapeutic levels of all ARTs in the combinations. Medications specifically contraindicated with concomitant use of these other ARTs are prohibited.
  - a. Cisapride, dihydroergotamine, ergonovine, ergotamine, methylegonovine, midazolam, pimozone, triazolam or any other major CYP3A4 substrates

## **Toxicity Management**

Guidelines for grading the severity of adverse experiences are based on DAIDS criteria for grading severity of adverse events from December 2004 (Appendix 1).

Decisions to temporarily withhold therapy because of an adverse experience will be reviewed on a case-by-case basis by the investigator. The investigator should consider temporarily withholding therapy if the severity of the adverse experience is Grade 3 or above and/or if clinically indicated. The decision to interrupt therapy should take into account the patient's baseline laboratory values and any concomitant medications that could be contributory. At the discretion of the investigator, therapy may generally be reinstated when laboratory abnormalities or clinical adverse events return to near normal baseline values.

If after re-initiation of study therapy, there is a recurrence of the laboratory abnormality or clinical adverse event, consideration should be given to permanently discontinuing all study therapy. In general, when a clinical or laboratory adverse event occurs which requires interruption of study therapy, study drug should be interrupted to avoid having a patient receive suboptimal therapy which may predispose them to the development of resistance. In general, study medication should be restarted at full dose concomitantly. Whenever study drug is interrupted due to a study drug related adverse experience, the interruption should be reported on the case report form.

### **3.2.2 Diet**

Patients can take Raltegravir without regard to food consumption. All other antiretroviral drugs in the study will be taken with food.

### **3.2.3 Procedures**

The investigator will follow the patients according to the standard of care. Patients will in addition undergo all the study visits and procedures indicated in the flow chart. Assessment of serious adverse experiences will be made at these visits. All serious adverse events must be immediately reported to the Principal Investigator. In addition, adverse experiences that are drug related and result in Grade 3 or above laboratory toxicity, lead to treatment interruption, or discontinuations (with the reasons for discontinuation) must be reported to the Principal Investigator. Laboratory assays are to be evaluated by the investigator's local laboratory.

Any patient who becomes pregnant during the course of the study must immediately be discontinued from all study medication. All pregnancies must be reported immediately to the Principal Investigator and must be followed to the completion/termination of the pregnancy. The outcome of all pregnancies must be reported to the Principal Investigator.

#### **3.2.3.1 Informed consent**

The investigator must obtain documented consent from each potential patient in biomedical research or when an investigational drug is administered to patients in a clinical study, prior to any study related procedures being performed.

**IRB Approved**

**06/24/13**

[figure not shown]

Consent must be documented by the patient's dated signature on a Consent Form along with the dated signature of the person conducting the consent discussion. A copy of the signed and dated consent form should be given to the patient before participating in the trial.

### **3.2.3.2 Assignment of Baseline Number**

For identification purposes during the screening, each patient will be assigned a unique baseline number. He/she will then be randomly assigned to one of the two study groups.

Patients who are HIV seropositive and are antiretroviral naïve (defined as having previously received no antiretroviral therapy or fewer than 7 days of therapy) will be considered for enrollment in this study. The investigator shall discuss with each patient the nature of the study, its requirements, and its restrictions. Written informed consent must be obtained prior to performing any study-specific procedures. Laboratory safety assessment will be performed per study flow chart (Section 1.6). Female patients of childbearing potential will have a pregnancy test performed prior to the study start date. Women who are found to be pregnant will be excluded from the study.

All patients will be asked about prior use of antiretroviral agents and the length of time on therapy with these agents AIDS defining illness, hepatitis B and C history, and genotype and phenotype data. This information will be recorded on the appropriate case report form. If prior genotypic or phenotypic antiretroviral resistance testing is not available, testing must be performed at screening.

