| Fasting Blood Glucose                   | X          | X         | X        | X        | X        | X         | X         | X         | X         | X         | X   |
| Fasting Insulin Level                   | X          |           |          |          |          | X         |           | X         |           | X         | X   |
| Fasting Lipid Panel                     | X          | X         | X        | X        | X        | X         | X         | X         | X         | X         | X   |
| Urinalysis                              | X          | X         | X        | X        | X        | X         | X         | X         | X         | X         | X   |
| Lipoprotein Analysis                    | X          |           |          |          |          | X         |           | X         |           | X         | X   |
| LFTs                                    | X          | X         | X        | X        | X        | X         | X         | X         | X         | X         | X   |
| Hepatitis Serology                      | X          |           |          |          |          |           |           |           |           |           |     |
| HIV Genotyping                          | X          |           |          |          |          | X         |           |           |           |           |     |
| HIV Phenotyping                         | X          |           |          |          |          | X         |           |           |           |           |     |
| Adverse Events                          | X          | X         | X        | X        | X        | X         | X         | X         | X         | X         | X   |
| Obtain Plasma Sample for Storage        | X          | X         | X        | X        | X        | X         | X         | X         | X         | X         |     |
| Serum Pregnancy Test                    | X          | X         | X        | X        | X        | X         | X         | X         | X         | X         | X   |
| Randomization                           |            | X         |          |          |          |           |           |           |           |           |     |
| Dispense Darunavir/Raltegravir          |            | X         |          | X        | X        | X         | X         | X         | X         | X         |     |

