## 2.2 SUBJECT/PATIENT INCLUSION CRITERIA

Inclusion Criteria:

- The patient has documented HIV-1 infection.
- The patient is at least 18 years of age.
- Antiretroviral naive, defined as 7 days or less of ARV treatment at any time prior to study entry.
- HIV viral load greater than 5,000 copies/ml prior to study entry.
- Willing to use acceptable forms of contraception
- Hepatitis B surface antigen (HBsAg) negative at study entry

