## 2.3 SUBJECT/PATIENT EXCLUSION CRITERIA

**IRB Approved**

**06/24/13**

[figure not shown]

Exclusion Criteria:

- Patient is current participant in a Raltegravir trial or in trials involving any of the other study medications (Darunavir, Tenofovir or Emtricitabine)
- Immunomodulators (e.g., interleukins, interferons, cyclosporine), HIV vaccine, systemic cytotoxic chemotherapy, or investigational therapy within 30 days prior to study entry. Individuals receiving either stable physiologic glucocorticoid doses, corticosteroids for acute therapy for pneumocystis pneumonia, or a short course (2 weeks or less) of pharmacologic glucocorticoid therapy will not be excluded.
- Known allergy/sensitivity to study drugs or their formulations
- Patient has a condition (including but not limited to active alcohol or drug use) that, in the opinion of the investigator, may interfere with patient adherence or safety
- Patient with acute hepatitis due to any cause or clinically significant chronic liver disease (defined as Child-Pugh Class B or C; see table 3)
- Patient has severe renal insufficiency defined as a calculated creatinine clearance at time of screening <30 mL/min, base on Cockcroft/Gault equation which is as follows (and 0.85 X this value for females):
  - $CrCl \text{ (mL/min)} = [(140 - \text{Age}) \times \text{Weight (in Kg)}] / 72 \times \text{Serum Creatinine (mg/mL)}$
- Serious illness requiring systemic treatment or hospitalization. Patients who have completed therapy or are clinically stable on therapy for at least 7 days prior to study entry are not excluded.
- Known clinically relevant cardiac conduction system disease
- Patient requires or is anticipated to require any of the prohibited medications noted in the protocol
- Current imprisonment or involuntary incarceration for psychiatric or physical (e.g., infectious disease) illness
- Pregnancy and Breastfeeding. Women who become pregnant during the study will be required to permanently discontinue their study regimens.

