## 2.4 STUDY DESIGN AND DURATION

This is a randomized, active Control, safety/efficacy study. All eligible patients (antiretroviral naïve,) will be randomized (1:1) into two treatment groups:

1. Group A: will receive Raltegravir + Ritonavir-boosted Darunavir
2. Group B: will receive Tenofovir + Emtricitabine + Ritonavir-boosted Darunavir

For analysis, patients will also be stratified according to baseline viral load (VL <100,000 or ≥100,000) and baseline CD4 count (<200 or ≥200).

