### Secondary Outcome Measures:

- Percentage of patients with serious adverse experience
- Percentage of patients with drug-related adverse experiences that result in grade 3 or above laboratory toxicity
- Percentage of patients with drug related adverse experiences that lead to treatment interruption
- Time from treatment dispensation to the first development of a Grade 3 or 4 sign, symptom, or laboratory abnormality that is at least one grade higher than at baseline
- Percentage of patients with HIV viral load levels less than 50 copies/ml at 24 and 48 weeks.
- Median CD4 count at 24 and 48 weeks and at virologic failure
- Median change in limb fat by DEXA at week 48
- Percentage of patients with occurrence of fasting hypertriglyceridemia (TG >400) or hypercholesterolemia (TC >240) at week 48
- HIV-1 drug resistance patterns at baseline and at time of virologic failure

For assessment of safety and tolerability, counts and percentages of patients with clinical or laboratory adverse experiences of the following type will be tabulated (1) serious adverse experience, (2) drug-related adverse experiences that result in grade 3 or above laboratory toxicity; (3) drug related adverse experiences that lead to treatment interruption; (4) drug related adverse experiences leading to discontinuation.

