### 3. PROTOCOL DETAILS

#### 3.1 RATIONALE

HAART regimens with the most experience in demonstrating virologic and immunologic efficacy – and therefore recommended by the DHHS for initial therapy of antiretroviral naïve patients – are those composed of 2 NRTI and 1 NNRTI or a boosted PI. Apart from limited data on PI monotherapy [1, 2], and switch studies [3], NRTI-free regimens have never been used on a significant number of patients for a significant amount of time. Such regimens have usually been found to have significantly lower virologic efficacy [1]. However, because of concerns about long-term drug toxicity, the development of drug resistance, and potential complications in pregnant women, it is imperative that other drug combinations, including NRTI-free regimens, be investigated as possible alternative initial regimens.

NRTI use is associated with significant toxicity, including mitochondrial dysfunction (mostly attributed to thymidine-analogue NRTIs): lipoatrophy, peripheral neuropathy, pancreatitis, and lactic acidosis [4]. There's also the risk of hypersensitivity reaction from Abacavir, and caution is needed when using Tenofovir in patients with renal failure. Recent data (including ACTG trials 5110, 5125s, and 5142) suggest that a switch to NRTI-free regimens might significantly improve the side-effect profile [3, 5]. NRTI-free arms had lower rates of lipoatrophy, but also higher rates of hypertriglyceridemia and a trend towards higher virologic failure rate [5]. The NRTI-free regimens in all these studies were Lopinavir with an NNRTI (Efavirenz or Nevirapine), and it's reasonable to expect that the use of a PI with a better metabolic profile than LPV/r might significantly improve the side-effect profile of such regimens.

A suggestion from these and other trial results is that NRTIs might be associated with other than the known complications, but these have been difficult to detect because there have been few long-term comparisons of NRTI-containing and NRTI-free regimens, and very few have been done on naïve HIV-infected patients [6]. Finding effective NRTI-free regimens would have a number of potential benefits including: 1) a significant expansion of therapeutic options; despite the growing number of antiretrovirals, treatment options might still be significantly limited in a patient with a number of baseline NRTI mutations [7] or poor NRTI tolerance; 2) potential avoidance of toxicities;

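### Baseline resistance results are collected but not used for eligibility, so patients with known tenofovir or emtricitabine resistance can enter the control arm and weaken it

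*Protocol*

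**What the plan says.** **Collection of the result.** Protocol 3.2.3.2 asks for genotype and phenotype data on all patients and adds: "If prior genotypic or phenotypic antiretroviral resistance testing is not available, testing must be performed at screening". The flow chart (1.6) has a row that begins "HIV Genotyping | X", with the mark in the screening column. The phenotyping row is marked in the same way.

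**Eligibility.** The nearest inclusion rule in 2.2 rests on treatment history: "Antiretroviral naive, defined as 7 days or less of ARV treatment at any time prior to study entry". The nearest exclusion in 2.3 is a discretionary one for a condition that, "in the opinion of the investigator, may interfere with patient adherence or safety". Neither list mentions resistance. Section 3.2.3.3 randomises patients who meet these requirements 1:1.

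**Other uses.** The secondary outcomes in 2.4 include "HIV-1 drug resistance patterns at baseline and at time of virologic failure". The analysis strata in 2.4 are baseline viral load and CD4 count, not resistance.

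**Rationale.** Section 3.1 notes that "treatment options might still be significantly limited in a patient with a number of baseline NRTI mutations [7] or poor NRTI tolerance".

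**The concern.** The two arms share boosted darunavir. They differ in raltegravir (Group A) versus tenofovir plus emtricitabine (Group B). Virus with reduced susceptibility to either NRTI can therefore impair only Group B's regimen.

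The hypothesis in 2.1.1 is that Group A's virologic efficacy is no lower than Group B's, and the power statement in 3.4 speaks of ruling out a 15% difference. In a comparison read that way, anything that lowers the control response makes the favourable conclusion easier to reach. What is at stake is assay sensitivity in the design sense: the ability of the trial to show that the test regimen is worse when it is.

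The rationale accepts that NRTI mutations can be present at baseline, so a rule based on treatment history does not by itself ensure susceptible virus. The information needed to deal with this is already collected before randomisation.

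**Working it through.** **Step 1. Can such a patient be randomised to Group B?** Set the rules side by side:

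- A resistance result is expected for each patient by screening (3.2.3.2 and 1.6).
- The inclusion list (2.2) covers HIV-1 infection, age, treatment history, viral load, contraception and hepatitis B. It has no resistance rule.
- The exclusion list (2.3) has no resistance rule, and its discretionary item concerns adherence or safety.
- Eligible patients are randomised 1:1 (3.2.3.3).

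So the written rules admit the patient and allocate him or her to Group B with probability one half.

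**Step 2. The plan's own figure.** Section 3.4 gives 40 per arm, 85% response in both arms, a 15-point difference and 80% power. Alpha is not stated. With unpooled variance:

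- SE = √(2 × 0.85 × 0.15 / 40) = 0.0798, and 0.15 / 0.0798 = 1.879.
- Power = Φ(1.879 − z). This is 46.8% at one-sided 0.025, 59.2% at 0.05, 72.5% at 0.10 and 80.0% at 0.15.

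The stated 80% is thus reached only at one-sided alpha 0.15. That is a separate matter and the present point does not depend on it. The same SE gives a 95% confidence interval half-width of 1.96 × 0.0798 = 15.6 points.

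**Step 3. Size of the effect.** Let q be the prevalence of relevant NRTI resistance and d the loss of response it causes in Group B. The protocol gives neither, so both are assumptions: q = 2%, 5%, 10% or 15%, and d = 10, 30 or 50 points.

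- Control response = 0.85 − q × d.
- Expected resistant controls = 40 × q.
- False conclusion: suppose Group A truly responds at 70%, which is 15 points below the control rate in patients with susceptible virus. The chance of ruling out a 15-point deficit at one-sided 0.025 is Φ((0.15 + 0.70 − pC)/SE − 1.96), where pC is the control response and SE = √(0.70 × 0.30/40 + pC(1 − pC)/40). It is 2.5% when pC = 0.85.

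| q | d (points) | Resistant controls expected | Control response | Fall (points) | False conclusion |
|---|---|---|---|---|---|
| 2% | 10 | 0.8 | 84.8% | 0.2 | 2.6% |
| 5% | 30 | 2 | 83.5% | 1.5 | 3.6% |
| 10% | 30 | 4 | 82.0% | 3.0 | 5.0% |
| 10% | 50 | 4 | 80.0% | 5.0 | 7.5% |
| 15% | 50 | 6 | 77.5% | 7.5 | 11.6% |

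Of the twelve combinations of q and d, nine give a fall of 3 points or less.

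**Step 4. Ceiling.** At 85% response, 15% fail anyway, so d cannot exceed 85 points. At 10% prevalence the largest possible fall is 0.10 × 0.85 = 8.5 points, or 3.4 of 40 patients. Even that requires every affected patient to fail while taking boosted darunavir, for which the protocol offers no support.

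**The case against.** The case on the other side has several parts.

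- **No bias.** A reader might infer that the comparison is biased. It is not: 1:1 randomisation spreads resistant patients over both arms in expectation, and the estimate is valid for the population enrolled. This stands. What remains is a weaker control, in a trial that calls itself a pilot estimation study.
- **The testing is neither purposeless nor always new.** A reader might infer that a fresh test is compulsory for everyone and serves nothing. The text requires one at screening only when no earlier result exists, and the baseline result feeds a secondary outcome. Both stand, but neither governs who is randomised.
- **The objective does not promise a fully active control.** Section 2.1.2 compares with a named regimen, and the remark on NRTI mutations in 3.1 is made as an argument for NRTI-free treatment. Enrolling patients whatever their genotype is compatible with that. This stands as a matter of wording. It does not alter the direction in which control failures due to resistance would push the result.
- **The investigator can exclude.** The discretion in 2.3 covers adherence and safety. It does not mention drug susceptibility, so it is not a dependable safeguard.
- **The effect may be near zero.** It would be if resistance were rare or darunavir carried the regimen. This stands, and it limits the weight of the point.
- **An eligibility rule could be lopsided.** If the assay does not cover raltegravir, the rule protects the control drugs only. This stands and is met in the fix.

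**Conclusion.** The gap holds: a resistance result is collected before randomisation, no eligibility rule uses it, and patients with known reduced susceptibility to the control NRTIs can be allocated to Group B. The consequence is a possibly weakened control and lower assay sensitivity, in the direction that favours the hypothesis.

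Under the assumed ranges the control rate falls by 0.2 to 7.5 points. Most of that range is small against both the 15-point difference and the 15.6-point half-width. The figures rest entirely on assumed prevalence and loss of response. The false-conclusion rates further assume one-sided 0.025 and a true 70% response in Group A.

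The protocol does not support a claim that the estimate is invalid. Nor is the absence of a sensitivity analysis from the protocol a fault in itself, since that may sit in a statistical analysis plan that was not available. The point rests on the eligibility rules, which the protocol fixes, and it is a cheap improvement rather than a fatal flaw.

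**What to change.** Add to 2.3 an exclusion for documented baseline resistance to those study drugs that the assay covers, and make the result part of the week-0 eligibility check already in the flow chart. The sponsor should define which findings qualify and state whether raltegravir is covered.

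The check belongs before randomisation. The primary analysis takes only dosed patients and treats discontinuation as non-response (3.4), so acting on the result after open-label allocation could affect one arm more than the other.

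For patients already enrolled, report the primary endpoint also without those who had such resistance at baseline, in both arms.

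**Cost.** One eligibility line and a definition. The sample is taken 3 to 4 weeks before week 0; the protocol gives no turnaround time, so it is an assumption that the result is back by then. A few screened patients would be excluded and replaced, and the population becomes slightly narrower. If all patients with NRTI resistance are identified and excluded, the fall in control response calculated above becomes zero.
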